##### Patients’ psychological distress

Patients’ psychological distress will be measured with the HADS.

#### Mediator

##### Caregivers’ self-efficacy

Caregivers’ beliefs about their capacity to carry out caregiving tasks will be measured using the Revised Scale for Caregiving Self-Efficacy [52]. The original version of the instrument consisted of 15 items within 3 subscales; self-efficacy for obtaining respite, responding to disruptive patient behaviors, and controlling upsetting thoughts about caregiving. The disruptive patient behaviors scale is not suitable for our target population and is omitted.

Caregivers are asked to indicate on a scale of 0 (absolutely cannot do) to 100 (certainly can do) how confident they are with respect to items such as “how confident are you that you can control worrying about future problems that might come up with [patient]”. All subscales demonstrate strong internal consistency and adequate test-retest reliability [52]. We added 3 additional questions based on the Job Content Questionnaire aimed at the control that caregivers perceive over fulfilling the caregiver tasks [53].

#### Covariates

##### Caregivers’ social support

Caregivers’ experience of social support will be measured using the Multidimensional Scale of Perceived Social Support (MPSS) [54]. The MPSS consists of 12 items and is aimed at different sources of social support (family, friends, and significant others). The items are scored on a 7-point Likert scale ranging from 1 (very strongly disagree) to 7 (very strongly agree). The total score is calculated by adding up the scores of all items, resulting in a range of 12–84. A higher score indicates stronger social support, with scores ≥ 79 corresponding to an experience of strong support. MPSS has proven to be a psychometrically valid instrument, with good test-retest reliability and adequate validity among varying populations [54–56].

##### Caregivers’ satisfaction with relationship

Caregivers’ satisfaction with the relationship with the patient will be assessed using the Satisfaction Scale [57]. The questionnaire consists of 4 satisfaction items which are rated on a scale ranging from 1 (not satisfied) to 5 (satisfied). A total score is calculated by adding up the scores of the 4 items, with a higher score indicating more satisfaction with the relationship. The items refer to caregivers’ experience during the last month. The satisfaction scale shows reasonable internal consistency [58].

##### Patients’ behavioral changes

Behavioral changes in patients will be assessed with the Amyotrophic Lateral Sclerosis-Frontotemporal Dementia-Questionnaire (ALS-FTD-Q) [36]. The questionnaire asks the caregiver to compare the patient’s current behavior with his/her behavior 3 years ago. It consists of 25 items with a total score range of 0–100 (≥ 22 indicating mild behavioral changes and ≥ 29 corresponding to significant behavioral changes). The ALS-FTD-Q shows good internal consistency (Cronbach’s  alpha = 0.92) as well as construct validity [36].

##### Patients’ physical functioning

The physical functioning of patients will be assessed using the Amyotrophic Lateral Sclerosis Functional Rating Scale-Revised (ALS-FRS-R) [35]. The scale consists of 12 items with 0–4 point scores in order to measure limb, bulbar, and respiratory dysfunction. An example is the item “Walking” with answer scores 0 = normal to 4 = is unable to consciously move legs. Overall scores range from 0 to 48, with higher scores indicating better physical functioning. The ALS-FRS-R demonstrates strong internal consistency as well as construct validity [35]. This questionnaire will be completed by the caregiver.

##### Patients’ perception of being a burden

Patient’s own feelings of being a burden for the caregiver will be measured using one item of the Self Perceived Burden Scale (SPBS): “I feel that I am a burden to my caregiver” [59]. This statement is rated on a scale of how often patients feel this way, from “none of the time” (1) to “all of the time” (5). Higher scores indicate that the patients perceived themselves to cause a higher burden to their caregivers.

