### Study population

Caregiver-patient dyads will be recruited through a nationwide ALS/PMA database and via the website of the Dutch ALS Center. The study will also be announced on websites of ALS/PMA patient associations. Patient and inclusion criteria are 1) the caregiver is the partner of the ALS or PMA patient; 2) the caregiver is 18 years or older; 3) caregiver and patient are proficient in Dutch to fill out the questionnaires; 4) caregiver and patient have internet access. When patients are not able or not willing to complete online questionnaires, caregivers are still eligible to join the support program provided the patient consents. The inclusion criteria remain in force.

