Online module 3 Your resilience plan	• Dealing with continuous stress • Moments of relaxation • Using your sources	To make a resilience plan that may allow caregivers to maintain health during this stressful period by taking care of themselves.	• Acceptance • Mindfulness
Online module 4 What is really important	• Values in relationship • Values in life	To identify the values of the caregiver in different areas of life and to plan action to meet these values.	• Values • Commited action • Mindfulness
Online module 5 Moments of joy	• Positivity during difficult times • Celebrate the relationship	To seek, enjoy and cherish the positive moments in the relationship and in life.	• Committed action • Mindfulness
Online module 6 A good last period	• Life story of the patient • Communication in this last phase • Beautiful memories • Being grateful	To create a beautiful last period with the loved ones and to make memories with the patient for the future.	• Acceptance • Communicating about what really matters • Committed action • Mindfulness
Telephone call	• Any questions • Finish the support program	To offer support with regard to any issues and close the support program.	

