### Assessments

All quantitative assessments are self-report measures and will be administered online. Overviews of the questionnaires for caregivers and patients and their time of assessment are provided in Tables 2 and 3. Participants who discontinue the intervention will be asked to complete study follow-up assessments. Semi-structured qualitative interviews will be conducted by telephone.

**Table 2 Tab2:** Measurement overview caregivers

		Measurement^a^			
Outcome	Instrument	T0	T1	T2	T3
*Socio-demographics*					
Caregiver, patient, and care characteristics	iMTA Valuation of Informal Care Questionnaire	x			
*Primary outcome*					
Psychological distress	Hospital Anxiety and Depression Scale	x	x	x	x
*Secondary outcomes*					
Quality of life	Care-related Quality of Life −7 + Care-related Quality of Life - VAS	x	x	x	x
Burden	Zarit Burden Interview + Self-Rated Burden scale	x	x	x	x
*Mediator*					
Self-efficacy	Revised scale for caregiving self-efficacy	x	x	x	x
*Covariates*					
Satisfaction with relationship	Satisfaction Questionnaire	x	x	x	x
Social Support	Multidimensional Scale of Perceived Social Support	x	x	x	x
Behavioral changes patient	Amyotrophic Lateral Sclerosis-Frontotemporal Dementia- Questionnaire	x	x	x	x
Physical functioning patient	Amyotrophic Lateral Sclerosis Functional Rating Scale- Revised	x	x	x	x
*Evaluation*					
Evaluation intervention	Client Satisfaction Questionnaire + Self developed scale		x^b^		x^c^

^a^T0 = Baseline, T1 = 3 months, T2 = 6 months, T3 = 9 months

^b^only for the intervention group

^c^only for the wait-list control group

**Table 3 Tab3:** Measurement overview patients

		Measurement^a^			
Outcome	Instrument	T0	T1	T2	T3
*Secondary outcomes*					
Quality of life	McGill Single Item Scale	x	x	x	x
Psychological distress	Hospital Anxiety and Depression Scale	x	x	x	x
*Covariates*					
Self-perceived as burden	Self-perceived Burden Scale - 1 item	x	x	x	x

^a^T0 = Baseline, T1 = 3 months, T2 = 6 months, T3 = 9 months

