### Analyses

#### Statistical analyses

Descriptive statistics will be used to report demographic variables, clinical outcomes, and the use of the different modules. Group differences in primary and secondary outcomes will be compared with linear mixed model analyses, in which the mediator and covariates will be included. Statistical analyses will be performed primarily according to intention-to-treat and secondarily according to per-protocol principles. The intention to treat analyses will include data of all included caregivers, regardless of their adherence to the intervention or their missing data. In the per-protocol analyses we will only include caregivers who completed at least 4 modules (66.7%) and the T2 measurement. All hypotheses will be tested 2-sided, with a critical value of 0.05. Effect sizes on the primary outcome variable (HADS total) will be calculated with Cohen’s D using the means and pooled standard deviations of the two groups.

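### The group-comparison models include the mediator and all covariates, with no limit to baseline values or to caregiver-completed measures

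*Protocol article*

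**What the plan says.** The Statistical analyses section sets one rule for the primary and secondary outcomes: groups "will be compared with linear mixed model analyses, in which the mediator and covariates will be included".

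The Assessments section defines the terms:
- Mediator: caregiving self-efficacy, including added questions on perceived control (Table 2).
- Caregiver-completed covariates: relationship satisfaction, social support, ALS-FTD-Q and ALS-FRS-R (Table 2).
- Patient-completed covariate: "Self-perceived Burden Scale - 1 item" (Table 3). Its own section confirms that the patient's feeling of being a burden "will be measured using one item of the Self Perceived Burden Scale (SPBS").

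All of these are marked at every wave ("T0 = Baseline, T1 = 3 months, T2 = 6 months, T3 = 9 months").

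Three other statements bear on the point:
- Study population: "When patients are not able or not willing to complete online questionnaires, caregivers are still eligible to join the support program provided the patient consents".
- Statistical analyses: "The intention to treat analyses will include data of all included caregivers, regardless of their adherence to the intervention or their missing data".
- Randomization: allocation follows completion of the first assessment.

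**The concern.** **Loss of caregivers.** A likelihood-based mixed model copes with missing outcomes. It drops records with a missing covariate unless that covariate is imputed. If the patient item is in the caregiver HADS model, a caregiver whose patient answers nothing contributes nothing. That caregiver was knowingly admitted and is promised a place in the intention-to-treat analysis. The loss would probably be selective, since inability to complete questionnaires points to more impaired patients. If same-wave values are used, ratings of the patient's current state also end at death, even when the caregiver's HADS score is observed.

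**Over-adjustment.** Baseline values precede allocation, so the programme cannot affect them. Later values can be affected. The clearest case is the mediator, because feelings of control are the programme's declared route to lower distress. Relationship satisfaction is next: Table 1 has a module on communication and another whose goal is "To seek, enjoy and cherish the positive moments in the relationship and in life". Social support is plausible through contact with other caregivers on the platform. Adjusting for such values estimates what remains after part of the benefit is removed, not the total effect of offering the programme.

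**Working it through.** **1. Starting point.** Inputs from the Sample size section: difference 3.65, SD 7.3, alpha 0.05 (two-sided per Statistical analyses), power 80%, 140 dyads, 20% attrition. The standardised difference is 3.65 / 7.3 = 0.50.

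The plan's own figure comes first: n per group = 2 × (1.960 + 0.842)² / 0.50² = 62.8, so 63 per group and 126 in total (64 and 128 by t-test). The stated 58 per group and 116 in total do not reproduce; 58 per group gives 76.8% power. That is a separate matter, and 116 is not used below.

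Completers: 140 × 0.80 = 112, or 56 per group.
Power = Φ(0.50 × √(56/2) − 1.960) = Φ(0.686) = 75.4%.

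**2. Patient item in the caregiver model, no imputation.** The documents give no opt-out rate, so q is assumed. Analysed total = 112 × (1 − q), with the same power formula.

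| Assumed opt-out q | Analysed | Power |
|---|---|---|
| 0% | 112 | 75.4% |
| 10% | 100.8 | 70.9% |
| 20% | 89.6 | 65.8% |
| 30% | 78.4 | 60.0% |

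**3. Post-baseline values in the model.** The share m of the effect carried by these variables is also assumed. Adjusted effect = 3.65 × (1 − m), at 112 completers.

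| Assumed share m | Adjusted effect (points) | Power |
|---|---|---|
| 10% | 3.29 | 66.3% |
| 30% | 2.56 | 45.7% |
| 50% | 1.83 | 26.2% |

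With q = 20% and m = 30% together, power is 38.1%.

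**4. Simulation check.** 2,000 trials were simulated with 56 per group, a true difference of −3.65 points, and 30% of it passing through a covariate measured after baseline. In the two adjusted analyses, 20% of records were removed at random.

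| Model | Mean estimate |
|---|---|
| Unadjusted, all records | −3.63 |
| Adjusted for the baseline covariate | −3.64 |
| Adjusted for the post-baseline covariate | −2.53 |

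The last figure agrees with 3.65 × 0.70 = 2.56. Baseline adjustment left the estimate where it was, so the harm comes from entering later values and not from measuring them. Because removal was random, the simulation does not show any bias from selective loss.

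**The case against.** The best defence is that one condensed sentence covers several models. The patient item appears only in Table 3, beside the patient outcomes. It is natural to pair each table's covariates with that table's outcomes. On that reading no caregiver is lost, because a patient who answers nothing has no patient outcome either. The ALS-FTD-Q and ALS-FRS-R are completed by the caregiver, so patient opt-out does not touch them. Handling of missing covariates is commonly left to an analysis plan, which is not shown here.

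On over-adjustment, a measurement schedule does not specify a model. Two of the covariates are also stratification factors measured before allocation, which fits baseline adjustment. Loss of covariates at the patient's death arises only if same-wave values are used. The ALS-FRS-R is unlikely to respond to the programme. The social support scale asks about family, friends and significant others, so its link to peer contact is weaker than that of relationship satisfaction.

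The figures are also rough. Opt-out may overlap with the 20% attrition, which is counted in dyads. A two-group formula ignores the repeated measures and any precision gained from covariates.

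All of this stands as a limit on certainty. It does not remove the defect. The analysis sentence is a stated rule that covers every primary and secondary outcome and restricts neither wave nor respondent. It also names the mediator outright, and a mediator can account for an effect only through values measured after allocation.

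**Conclusion.** The rule is badly fixed and should be changed. Read literally, it conflicts with the admission of caregivers whose patients do not respond and with the promise to analyse every included caregiver. It also lets variables that the programme is meant to change into the estimate of its effect.

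A reader might go further and infer that caregivers will be dropped and the effect will be adjusted away. The documents do not support that. The first harm needs the patient item to be in the caregiver model and left unimputed. The second needs T1 to T3 values to be entered, and variables that respond to the programme.

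Under those conditions the size is material: power of about 71% to 60% instead of 75% for an assumed 10% to 30% opt-out, and an estimate of about 2.5 instead of 3.6 points if 30% of the effect runs through the adjusted variables. Neither the opt-out rate nor that share is in the documents. Confidence is moderate, because both harms depend on how the sentence is implemented.

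**What to change.** Amend the Statistical analyses section in two sentences:
- The caregiver group-comparison models use only caregiver-completed T0 values as covariates, and the patient's self-perceived burden item is left out of them.
- T1 to T3 covariate values and the mediator are reserved for separate exploratory or mediation analyses.

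This needs no new data, since the caregiver's T0 assessment comes before randomisation. Patient non-response then no longer affects the caregiver models. The cost is that later covariate values inform exploratory models only.

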#### Evaluation of the intervention

##### Satisfaction with received support

To measure the satisfaction of the caregiver for the support they received, the 8-item Client Satisfaction Questionnaire (CSQ-8) is used [60]. All items are scored on a 4-point scale ranging from 1 to 4. Response options differ from item to item. An example is “How satisfied are you with the amount of help you have received?” (for which the response options range from 1 = “Quite dissatisfied” to 4 = “Very satisfied”). An overall score is calculated by summing and ranges from 8 to 32, with higher scores indicating greater satisfaction. The Dutch translated version of the questionnaire shows high internal consistency (.91) [61].

##### Evaluation support program

Additionally, a scale to evaluate the intervention was developed. The participant is asked to rate the intervention in general and the different components of the intervention such as the psychological exercises, contact with the psychologist who provided the feedback and contact with other informal caregivers. Participants are asked to rate every component on a 0–10 scale; the questionnaire consists of 9 questions.

##### Experiences with support program

Semi-structured interviews to explore the experiences of the caregivers with the support program will be carried out after subjects complete the support program. Participants will be selected via purposive sampling on demographic variables (age, sex, disease stage patient). Interviews will be held by a researcher, using a topic list with the following topics: experiences with support program, user-friendliness, use of the support program, valuable, missing and redundant elements of the support program and recommendations for change. The interviews will last approximately 1 h and will be recorded. Participants will be included until data saturation is reached.

#### Demographics and description of the care situation

##### Demographics and care situation

The iMTA Valuation of Informal Care Questionnaire (iVICQ) is a questionnaire which facilitates an accurate description of providing informal care and its effects on informal caregivers [62]. We used the sections of the background information of patients and caregivers, the informal care situation and questions to economically validate informal care as a directory for our questions regarding these subjects.

#### Questions to assess the working mechanism of the support program

The support program aims to improve feelings of control over caregiving and reduce psychological distress. Therefore, at the end of every online module, the caregiver is asked two questions about “feelings of control over executing caregiving tasks” and “the level of distress they experience”, at that moment on a VAS scale [63].

#### Monitoring adherence to the intervention modules

In order to assess the use of and the adherence to the online modules we will collect log data of the participants such as the frequency of logging in, the duration of logging in, which parts of the modules are downloaded and which functions are used.

### Data management

All personal data will be coded, removed from the data for analysis and stored separately. Only designated research staff will have access to the keys linking the data with the personal information. The research team will have access to the final dataset. Data management and monitoring of the trial will be performed by qualified personnel according to standard operation procedures of the Brain Center Rudolf Magnus, University Medical Center Utrecht.

### Analyses

#### Statistical analyses

Descriptive statistics will be used to report demographic variables, clinical outcomes, and the use of the different modules. Group differences in primary and secondary outcomes will be compared with linear mixed model analyses, in which the mediator and covariates will be included. Statistical analyses will be performed primarily according to intention-to-treat and secondarily according to per-protocol principles. The intention to treat analyses will include data of all included caregivers, regardless of their adherence to the intervention or their missing data. In the per-protocol analyses we will only include caregivers who completed at least 4 modules (66.7%) and the T2 measurement. All hypotheses will be tested 2-sided, with a critical value of 0.05. Effect sizes on the primary outcome variable (HADS total) will be calculated with Cohen’s D using the means and pooled standard deviations of the two groups.

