**Methods:**

This study is a randomized controlled trial using a wait-list control design. One hundred and forty caregiver-patient dyads, recruited from a nationwide database and through the website of the Dutch ALS Center, will be either randomized to a support program or a wait-list control group. The blended intervention is based on Acceptance and Commitment Therapy and consists of 1 face-to-face contact, 6 online guided modules and 1 telephone contact. The intervention can be worked through in 8 weeks. The effectiveness and the participants’ satisfaction with the intervention will be evaluated using a mixed method design. Caregivers and patients will be asked to fill in questionnaires on 4 occasions during the study: baseline, 3 months, 6 months and 9 months. The main study outcome is the psychological distress of the caregiver assessed with the Hospital Anxiety and Depression Scale. Secondary outcomes are caregiver burden, caregiver quality of life, quality of life of the patient and psychological distress of the patient. Group differences in primary and secondary outcomes at 6 months will be compared with linear mixed model analysis. In a subgroup of caregivers we will explore experiences with the support program through semi-structured interviews. Usage of the online modules will be logged.

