In this study, we will investigate the effect of a blended support program in which face-to-face contact and e-health will be combined. The support program is based on Acceptance and Commitment principles and focuses particularly on the needs of ALS and PMA caregivers. This support program aims to diminish caregivers’ psychological distress by increasing their feelings of control in fulfilling the caregiving tasks for patients with ALS or PMA.

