### Randomization

After completing the first assessment, dyads will be randomized into the wait-list control or experimental condition by the researchers according to a computerized programmed randomization scheme. Randomization will be stratified for the degree of functional impairment of the patient (Amyotrophic Lateral Sclerosis Functional Rating Scale-Revised, using the cut off score for severe disabilities ≥ 24) [34, 35], presence of behavioral problems of the patient (Amyotrophic Lateral Sclerosis-Frontotemporal Dementia-Questionnaire, using the cut off score for mild behavioral changes ≥ 22) [36] and gender of the caregiver.

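### The model for the group comparisons includes the program's own mediator and does not limit covariates to baseline values, so its group coefficient need not be the program's total effect on distress

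*Protocol article*

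**What the plan says.** The Statistical analyses section gives one specification for comparing the groups: "Group differences in primary and secondary outcomes will be compared with linear mixed model analyses, in which the mediator and covariates will be included".

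Table 2 lists self-efficacy under the heading Mediator. The section on caregivers' self-efficacy explains that the scale is extended by three items "aimed at the control that caregivers perceive over fulfilling the caregiver tasks". The Background states the intended mechanism: "This support program aims to diminish caregivers’ psychological distress by increasing their feelings of control in fulfilling the caregiving tasks". The measured mediator and the declared mechanism are therefore the same construct.

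Tables 2 and 3 schedule the mediator and every listed covariate at all four assessments ("T0 = Baseline, T1 = 3 months, T2 = 6 months, T3 = 9 months"). Randomization comes after the first of these: "After completing the first assessment, dyads will be randomized into the wait-list control or experimental condition". Values from T1 onward are therefore post-randomization. The text does not say which of them enter the model.

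The Abstract describes the same comparison without naming a mediator: "Group differences in primary and secondary outcomes at 6 months will be compared with linear mixed model analysis". The Sample size section is built on a 3.65-point difference between groups at T2 with SD 7.3. Cohen's d is to be computed from the group means and pooled SDs.

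**The concern.** A randomized comparison estimates what assignment to the program does to distress by every route. Holding constant a variable that the program is designed to change removes the part of the effect that travels through that variable. Here that variable is the program's stated route. The result is a contrast between caregivers with equal self-efficacy, and randomization does not protect that contrast. Including all caregivers under intention-to-treat settles who is analysed; it does not repair this.

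The same question arises for covariates that the program could move. Relationship satisfaction is the clearest case, since one module has the goal "To seek, enjoy and cherish the positive moments in the relationship and in life". The patient's physical functioning and behavioral changes describe the disease and are less likely to respond to a caregiver program.

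The article would also answer two different questions side by side. The sample size and Cohen's d concern the total difference between groups, while the hypothesis test would concern something else. A d near 0.5 could appear next to a non-significant test, with no guidance on which one answers the trial's objective.

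**Working it through.** **Inputs from the article.** Difference 3.65, SD 7.3, alpha 0.05 two-sided, 58 per group (116 in total).

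**Inputs assumed, not in the article.** The share P of the effect that is mediated (0 to 1) and the within-arm correlation ρ between mediator and HADS (0.3 to 0.7 in absolute value). The signs are set so that benefit is positive.

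**Step 1: the plan's own figure.** d = 3.65 / 7.3 = 0.50. The number per group is 2 × (1.96 + 0.84)² / 0.50² = 62.8, so 63 per group or 126 in total (128 with the t distribution). The stated 116 is not reproduced. At 58 per group, power is 76.8% by the normal approximation and 76.1% by the t-test. This is a separate matter; it serves here only as the reference power for a model without the mediator.

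**Step 2: model.** With both variables scaled to a within-arm SD of 1:
- M = aA + u and Y = c′A + bM + e
- total effect c′ + ab = 0.50
- b = ρ, a = 0.50P/ρ, c′ = 0.50(1 − P)

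With M measured at the outcome visit in the regression, the group coefficient is c′, and
- SE = √[(1 − ρ²) / (116 × 0.25 × (1 − R²))], where R² = 0.25a² / (0.25a² + 1)
- power = Φ(c′/SE − 1.96) + Φ(−c′/SE − 1.96)

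**Step 3: one case in full (ρ = 0.5, P = 0.5).** a = 0.50 and R² = 0.0625 / 1.0625 = 0.059. SE = √[0.75 / (29 × 0.941)] = 0.166. c′ = 0.25, which is 0.25 × 7.3 = 1.82 points. c′/SE = 1.51, so power is about 33%.

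**Step 4: range.**

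| Share mediated | Estimate (points) | Power, ρ = 0.3 | ρ = 0.5 | ρ = 0.7 |
|---|---|---|---|---|
| 0% | 3.65 | 81% | 88% | 97% |
| 25% | 2.74 | 55% | 64% | 80% |
| 50% | 1.82 | 26% | 33% | 46% |
| 75% | 0.91 | 9% | 11% | 15% |
| 100% | 0.00 | 5% | 5% | 5% |

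A simulation at ρ = 0.5 (4,000 runs) agrees: 2.73, 1.82, 0.91 and 0.00 points with 62%, 31%, 11% and 5% power for 25%, 50%, 75% and 100% mediated.

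**Step 5: baseline value only.** In the same simulation, with an assumed weight of 0.6 linking the T0 mediator to its T2 value, adjusting for T0 alone leaves the estimate at 3.65 points with about 80% power. Without any mediator it is 3.65 points with 76.5%. The problem arises only from post-randomization values.

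**Step 6: unmeasured confounding of mediator and outcome.** Let U add hU to M and gU to Y. The adjusted group coefficient becomes c′ − a·g·h / (1 + h²). With a = b = 0.5, total 0.50 and direct 0.25:
- g = 0.4, h = 0.5 gives 0.25 − 0.08 = 0.17
- g = −0.4, h = 0.5 gives 0.25 + 0.08 = 0.33
- g = −1.5, h = 1.0 gives 0.25 + 0.375 = 0.625 (simulated 0.62), which exceeds the total effect

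The adjusted coefficient can therefore fall below the direct effect or rise above the total effect.

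**The case against.** The strongest reply is that the article does not say what is being feared. It never states that T1 to T3 values of the covariates enter the model; Table 2 is a measurement schedule, not a model specification. Which time point of a covariate is used is the kind of detail an article leaves to the full protocol or the analysis plan. This stands. A reader might infer that the model adjusts for re-measured covariates, but the document supports only that it does not exclude them.

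A reader might also infer that the primary test is biased toward no effect. That direction holds only if the program acts through control as intended and nothing unmeasured drives both mediator and outcome. Step 6 shows that otherwise the coefficient can go either way. Nor is loss of power certain: at a correlation of 0.7 with 25% mediated, power is 80%, above the unadjusted 76–77%, because the mediator also removes residual variance. The estimate is still attenuated in that case.

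The Abstract names no mediator, the Statistical analyses section speaks of analyses in the plural, and Cohen's d would show the unadjusted difference. This softens the consequence but does not remove it, because d is not the hypothesis test and no test without the mediator is described. A reader might further conclude that mediation will never be properly tested. An analysis plan not shown may cover that, so it is no part of this point.

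The reply does not rescue the mediator itself. A variable acts as a mediator only through values that arise after assignment; a T0-only value would be a covariate, and the article lists covariates separately.

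**Conclusion.** The point holds in this form: the only model described for group differences includes the mediator, which is the program's declared pathway, and does not confine the covariates to baseline. On the natural reading that post-randomization mediator values enter, the group coefficient is not the total effect that the 3.65-point target and Cohen's d describe. This stands on the mediator alone, whatever is done with the covariates.

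The size cannot be fixed from the article. At 50% mediated and 58 per arm, the estimate is about 1.8 instead of 3.65 points, and power is about 26–46% instead of 76–77%. Under full mediation both the effect and the power above 5% vanish; under a small mediated share power may be kept or even gain. These figures assume linear mediation without confounding and a regression at a single time point, not the planned mixed model. They illustrate the problem and do not predict the result.

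**What to change.** Reword the sentence on the mixed models in three respects:

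1. Omit self-efficacy/control from the models that compare the groups on primary and secondary outcomes.
2. State that covariates enter those models at their T0 values only.
3. Place self-efficacy/control in a separate secondary mediation analysis that respects time order, for example the mediator at T1 and the outcome at T2. The estimation method can be left to the analysis plan.

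The analysis plan, if it exists, should carry the same wording. The change needs no new participants, visits or data. It costs a revised sentence and one secondary analysis, and should be made before the group comparison is run.
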